**Interim analyses {21b}**

The interim analysis will be conducted at midline and we will seek guidance from the ethics committee if the intervention is harmful to participants, i.e., if we observe a deterioration of primary outcomes.

**Methods for additional analyses (e.g., subgroup analyses) {20b}**

Further analysis will investigate if the effect of economic shocks on STIs and HIV varies depending on (1) women’s characteristics, (2) the person affected by the shocks (3) the type of shocks (e.g., illness, job loss), (4) the intensity of the shock and (5) available coping strategies (e.g., savings).

To explore the robustness of the cost-effectiveness deterministic and probabilistic sensitivity analysis will be conducted to explore the impact of uncertainty of parameter estimates, assumptions and model structure on the results.

**Methods in analysis to handle protocol non-adherence and any statistical methods to handle missing data {20c}**

Non-compliance issues will be investigated by estimating the local average treatment effect (LATE).

In addition, we will enquire about cases of STIs that were untreated at baseline and will also provide evidence of the impact of the intervention by removing participants who test positive at midline and endline because they did not take their treatment at baseline.

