**Primary outcome measure**

Measured using questionnaires developed by the study team where not otherwise stated at 1, 6 and 12 months:

1. STI acquisition measured using % test positive for syphilis, % test positive for chlamydia, % test positive for gonorrhoea. STI symptoms prevalence measured using % who had any symptoms of STI in the last 30 days: vaginal discharge, lower abdominal pain outside of diarrhoea or menstrual period, wound or ulcer on genitals, burns during urination, swelling in the groin, itching in the genital area, pain during the sexual act, bleeding outside of period

2. HIV status measured using % testing HIV positive

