**Sample size {14}**

The baseline study has recruited 1,508 unmarried girls and young women engaging in transactional (753) and commercial (755) sex in Yaoundé, Cameroon. Currently, 1,147 participants have been randomised via participatory randomisation, 568 participants allocated to the control arm and 579 allocated to the treatment arm. To maximise statistical power, STI-positive participants receive free treatment at baseline to start the trial with an STI-free cohort. Participants will also receive free treatment at midline to allow for the possibility to observe more than one STI per participant over the trial period. Free treatment will also be provided at endline for ethical reasons. Assuming that 20% of participants will get at least one STI over the trial period, this sample size is sufficient to show a decrease of 30% (6 percentage points) in the incidence of any STI in the treatment group assuming 80% power and a significance level of 5%. To conduct analysis separately among the sub-samples of those engaging in commercial and transactional sex, the MDE is a ~40% reduction (8.3 percentage points) in STI incidence. Assuming an HIV incidence of 4% over the trial period, the sample size would allow the detection of a decrease of 65% in HIV incidence (2.6 percentage points).

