The procedures for each test are as follows. For HIV, serological testing will be based on a venous blood draw and follows national procedures, including both pre-and post-test counselling. HIV testing utilised dual rapid testing (Alere Determine ^TM^ HIV – ½ and OraQuick HIV – ½ ) based on the national testing protocol (Figure 2). At midline and endline, participants with undetermined tests will be referred to the military hospital of Yaoundé for an ELISA test. Patients who test positive will be linked into care.

Figure 2: HIV testing algorithm based on Cameroon national protocol

Syphilis testing will utilize rapid VDRL and Treponema pallidum hemagglutination assays (TPHA) for the detection of syphilis antibodies and classification of primary, active and past infection (Figure 3). The testing algorithm will be based on the national protocol, but FTA-ABS is not available in Cameroon for confirmatory testing. Subsequently, we will not exclude false-positive VDRL tests which will be considered positive. For midline and endline we will only consider active cases of syphilis. Following the blood draw, participants received post-test counselling until results were available 30–40 minutes after testing. Participants who test positive will receive treatment for free. We will contact them to find out if the treatment was taken and, for those who have a partner, to understand if they provided information about their infection to their partner.

Figure 3: Syphilis testing algorithm adapted from the Cameroon national protocol

Chlamydia testing will utilize Chlamydia Rapid Test Kit on vaginal swabs and include pre-and post-test counselling. A swab specimen collected from the patient will be treated with an extraction reagent. The Chlamydia rapid test dipstick is immersed in the extraction sample. The liquid migrates through the absorbent area and along the membrane on the Chlamydia rapid test. As the mixture flows along the membrane of the Chlamydia rapid test, the complex is captured by the antibody immobilized in the test zone (T) of the membrane, producing a visible rose-pink colour band and at the same time in the control zone (C). A rose-pink line in the control zone (C) indicates the Chlamydia rapid test is working properly. When only a control line appears with no test line, the Chlamydia trachomatis antigen has not been detected and the Chlamydia rapid test result is considered negative.

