**Statistical methods**

**Statistical methods for primary and secondary outcomes {20a}**

All statistical analyses will be conducted using STATA. Descriptive statistics will first be used to summarise participant characteristics between the study groups. To investigate the effect of health insurance on primary and secondary outcomes, the analysis will use an intention-to-treat (ITT) approach where participants will be analysed in their allocated randomised study group. If there are non-compliers, i.e., participants and economic dependents who do not use the health insurance product when sick, we will also estimate the local average treatment effect (LATE). To investigate the effect of health insurance on primary and secondary outcomes, baseline characteristics will be compared for the treatment and control groups and determine whether there is differential attrition between the two groups. Outcomes for the treatment versus the control group will then be compared accounting for any baseline or attrition differences using ordinary least squared. The analysis will be conducted for all women and then separately for women engaging in transactional and commercial sex separately. A causal mediation analysis will be conducted to assess how much of the effect of health insurance on STI and HIV acquisition operates through risky sexual behaviours.

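### The supplementary analysis in {20c} drops women untreated at baseline only if they later test positive, so membership of the analysis set depends on the primary outcome

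*Protocol*

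**What the plan says.** The Sample size section {14} explains why baseline infections are treated: "STI-positive participants receive free treatment at baseline to start the trial with an STI-free cohort". It adds a second treatment point: "Participants will also receive free treatment at midline to allow for the possibility to observe more than one STI per participant".

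The primary outcome section defines the endpoint by test result: "STI acquisition measured using % test positive for syphilis, % test positive for chlamydia, % test positive for gonorrhoea". The main analysis is fixed in {20a}: "the analysis will use an intention-to-treat (ITT) approach where participants will be analysed in their allocated randomised study group".

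Section {20c} first offers the local average treatment effect for non-compliance. It then continues: "In addition, we will enquire about cases of STIs that were untreated at baseline", and says that the effect of the intervention will also be shown by "removing participants who test positive at midline and endline because they did not take their treatment at baseline".

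On uptake, the syphilis paragraph of {18a} says: "We will contact them to find out if the treatment was taken". No other section replaces or qualifies the exclusion rule.

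**The concern.** The aim is sound. A positive test at month 6 or 12 that is left over from an untreated baseline infection is not an acquisition, and a sensitivity analysis that sets such cases aside is reasonable.

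The rule as written does something else. Take two women who were both positive at baseline and both left the infection untreated. If one is positive at follow-up she is removed; if the other is negative she stays and counts in the denominator. Eligibility therefore depends on the variable being compared, and removals can only lower an arm's STI rate.

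The rule also needs a causal attribution, that the later positive occurred *because* baseline treatment was not taken. The chlamydia and gonorrhoea rapid tests in {18a} give a line or no line, and the syphilis algorithm classifies the stage of infection. Neither separates an infection that persisted from one acquired again. At endline the attribution is weakest, because free treatment has also been given at midline.

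At stake is whether this analysis can be read as a check on the main result, or whether it moves the arm difference by its own construction.

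**Working it through.** The protocol gives no figure for this analysis, so there is none to reproduce. The check is the algebra of the rule.

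**Inputs from the protocol.** Follow-up positivity of 20%, from {14} ("Assuming that 20% of participants will get at least one STI over the trial period"); target difference 6 points (20% against 14%); 568 control and 579 treatment participants randomised.

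**Assumed inputs, not in the protocol.**
- *b*, baseline STI prevalence: 10, 20 or 30%.
- *u*, share of baseline-positive women left untreated: 10 to 30%.
- *q*, probability that an untreated woman is positive at follow-up: 20, 50 or 80%.
- *p*, probability that anyone else is positive: 20% in both arms (no true effect).

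**Formulas**, with f = b × u:
- Intention-to-treat rate = f·q + (1 − f)·p
- Rate under the {20c} rule = (1 − f)·p / (1 − f·q)
- Rate if all untreated women are excluded whatever their later result = p

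**Step 1, direction.** Each removal takes one from both numerator and denominator. In the control arm, 0.20 × 568 = 113.6 events; removing 10 gives 103.6 / 558 = 18.6%. This shows only the direction within one arm.

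**Step 2, equal untreated shares and equal q.** Both arms fall together and the difference stays at 0. With q = 20% the common rate falls from 20% to 19.8% (b = 10%, u = 10%) or as far as 18.5% (b = 30%, u = 30%).

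**Step 3, untreated share 30% in one arm and 10% in the other.** For b = 30%, q = 20%:
- u = 30%: f = 0.09; 0.91 × 0.20 / (1 − 0.018) = 0.182 / 0.982 = 18.53%
- u = 10%: f = 0.03; 0.97 × 0.20 / (1 − 0.006) = 0.194 / 0.994 = 19.52%
- Spurious difference: about 1.0 point.

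The same calculation over the grid gives these spurious differences, in percentage points:

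| b | q = 20% | q = 50% | q = 80% |
|---|---|---|---|
| 10% | 0.3 | 0.2 | 0.1 |
| 20% | 0.65 | 0.4 | 0.2 |
| 30% | 1.0 | 0.6 | 0.3 |

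The sign depends on which arm has more untreated women. Excluding all untreated women gives 0 in every cell.

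**Step 4, equal untreated shares but different later positivity.** The insurance in {11a} covers consultation and pharmaceutical fees, and STIs are not among its listed exclusions, so insured women might more often be cured between visits. Assume f = 4% in both arms, with q = 60% in control and 30% in the insured arm:
- Control: 0.96 × 0.20 / (1 − 0.024) = 0.192 / 0.976 = 19.7%
- Insured: 0.192 / (1 − 0.012) = 0.192 / 0.988 = 19.4%

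The artefact is about 0.2 points in favour of insurance. Excluding all untreated women gives 20% in both arms.

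**The case against.** Five points can be made in defence of the rule.

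*The rule is narrower than it looks.* A reader might infer that anyone positive at follow-up is dropped. That is not what {20c} says: an untreated baseline infection is also required. This stands, but the outcome condition remains.

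*The analysis is supplementary.* A reader might infer that the trial's conclusion rests on it. It does not, because {20a} keeps every participant in the randomised group for the main analysis. This stands in full.

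*Baseline non-treatment should be balanced.* A reader might suppose that insured women more often took baseline treatment because they had easier access to care. The protocol does not support this. The retention section {18b} says STI treatment is free in both arms and paid by the project, not by the insurance. Recruitment began in June 2021, randomisation in October 2021 and insurance on 15 November 2021, so most failures to take baseline treatment should precede allocation. What remains is chance imbalance, and the route in step 4 through cure between visits.

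*The bias may be small, or even a correction.* A reader might assume ten or twenty more removals from the arm of 579 and obtain shifts of 1.4 or 2.9 points: (115.8 − 10)/569 = 18.6% and (115.8 − 20)/559 = 17.1%. Those excesses are arbitrary. With b = 20% and q = 20%, ten excess removals need an arm gap in non-treatment of 10/(579 × 0.20 × 0.20) = 43 points. Where untreated infections mostly persist, the rule can come nearer to the incidence effect than intention-to-treat. With b = 30%, q = 80% and untreated shares of 30% and 10%, intention-to-treat shows 25.4% against 21.8%, a difference of 3.6 points with no true effect on new infection, while the rule shows 0.3. This stands, and is why no direction can be claimed. It does not favour the rule over a baseline-only definition, which gives 0 in the same setting.

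*Who makes the attribution is not stated.* A reader might infer that it is made by staff who know the arm. Field staff do know the allocation, but the protocol does not assign them this task, and {17a} says data analysts are blinded. The supportable statement is only that the attribution cannot be verified from the tests described.

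Nor is this a detail left to a statistical analysis plan: the protocol states the condition for removal, and that condition includes the outcome.

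**Conclusion.** The point holds as a defect of one supplementary analysis. Membership depends on the primary outcome, every exclusion deletes an event, and the stated cause cannot be established from the planned tests.

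Over the ranges tried for unequal untreated shares, the spurious arm difference is about 0.1 to 1.0 points against a 6-point target, with no fixed direction. Under no true effect it is zero when the untreated share and these women's later positivity are equal across arms. It can arise with equal untreated shares if later positivity differs. All of these sizes rest on assumed prevalence, non-treatment and persistence, none of which the protocol gives. The main result is not in question.

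**What to change.** Replace the exclusion sentence in {20c} with a definition that does not use follow-up results. The sensitivity set would comprise women who were STI-negative at baseline, and women who were STI-positive at baseline and report having taken the baseline treatment. It would apply whatever the midline or endline result and identically in both arms. Uptake should be classified without reference to follow-up results or arm.

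The uptake enquiry is already planned in {18a} and {20c}. The promise of contact in {18a} sits in the syphilis paragraph, so the text should say that it covers every baseline STI. The protocol promises contact and enquiry only, so the definition should rest on reported uptake, not on uptake confirmed by a given date.

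In the illustrations above this returns a difference of 0.0 points under no effect and 6.0 points under 20% against 14%. The cost is one sentence and the loss from this set of a few untreated women who tested negative. The comparison still assumes that being untreated is unrelated to the risk of new infection, or is balanced between arms.

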**Plans to give access to the full protocol, participant-level data and statistical code {31c}**

Data and statistical code will be made openly available through the UCL data repository, subject to the ability to remove personally identifiable information. Data will be deposited with UCL research data repository (<https://www.ucl.ac.uk/library/research-support/research-data-management/ucl-research-data-repository>), where it will be given a Digital Object Identifier (DOI). The DOI will be cited in project reports and journal publications through a Data Access Statement or citation list. Metadata will also be made available to 3rd party research catalogues, such as <https://datamed.org/>. Qualitative responses will not be uploaded to this repository due to the potential to identify participants.

Anonymised data will be made openly available using a permissive licence, such as Creative Commons Attribution (CC-BY). If complete anonymity cannot be provided, it will be made available through a controlled access system. If data must be made available via controlled access, interested parties will be asked to provide information on their research (purpose, institutional affiliation, ethics approval) and sign a data sharing agreement indicating they will comply with the consent form and will not attempt to re-identify individuals. Access requests will be evaluated by the project team in the first instance. In cases where an access request is denied and the requester wishes to appeal, the request will be escalated to the UCL Research Governance Committee for consideration.

**Oversight and monitoring**

**Composition of the coordinating centre and trial steering committee {5d}**

There is no formal committee for the coordination and oversight of this trial. The PI will oversee and coordinate all aspects of the trial with the support of the project’s researchers. All decisions impacting the project protocol will be discussed with the lead researchers. The Advisory Group made up of experts internal (project staff from UCL and JHCP, partners from local CBOs RENATA and Femmes Horizons) and external (senior staff from UCL and JHCP) to the project, will be consulted at key decision points.

**Data monitoring {21a}**

There is no formal committee for monitoring data collected as part of the POWER project. Data monitoring will be undertaken by a researcher supervised by the PI. Questionnaire responses will be checked daily to determine any problems with the data collection instruments.

**Adverse event reporting and harms {22}**

The potential risks of participation in this trial are minimal. An adverse event will be defined as a participant becoming significantly distressed as a consequence of their involvement in the trial. All adverse events, as a consequence of participation in the POWER study, occurring after the entry into the study and until the end of the study will be recorded and will be treated on a case-by-case basis. In the event of an unanticipated adverse event that may cause direct harm or threat to the participants or others that are related to study implementation, the local JHU staff will notify the PI. Per protocol, an unanticipated event report will be submitted promptly to the Cameroon National Ethics Committee and the UCL ethics committee.

The study will not be providing any direct treatment. Participants who tested positive for HIV and/or STIs (Syphilis, Chlamydia, Gonorrhoea, Trichomoniasis) will be referred to POWER-supported health facilities with the capacity for follow-up treatment. They will also be referred to RENATA and Horizons Femmes (POWER CBOs) for pastoral support and advice.

We are not expecting any major adverse events from the implementation of these studies (socioeconomic survey, weekly SMS diaries, interviews, focus groups, laboratory testing activities). However, we will establish a procedure so that participants who require any medical attention as a consequence of laboratory testing activities, can have full access. Psychological stress may occur during the survey, interviews and focus group, as well as following the disclosure of HIV and STI results. Counsellors will be trained and made available to respond to stress resulting as part of the study.

During the study, we might have some minor adverse events such as syncope during blood drawing for laboratory testing. Patients will be informed of this risk. Laboratory technicians will be trained on how to deal with these minor events. An unlikely adverse event could be an infection at the site of the needle prick, the chance of which will be minimized through observing international standards of blood sample collection. The respondent will be properly counselled on how, where and when to seek treatment in case of such an incident.

Mild levels of stress may occur during interviews, as the questions cover sensitive topics and are likely to be unfamiliar to the respondents. Interviewers will be extensively trained to respond to stress resulting from any of these possible scenarios.

**Frequency and plans for auditing trial conduct {23}**

The PI meets weekly with researchers conducting the daily activities of the trial online to discuss and review trial progress, and at least monthly with the full investigator team. Any adverse events or issues in trial progress will be promptly communicated with the investigator team at these meetings or between meetings if necessary. Progress to the trial funder will be reported annually. Any trial protocol amendments will be reported to the University College London Research Ethics Committee and National Ethics Committee in Cameroon. The Steering Committee, comprised of key representatives from JHCP, RENATA, HF, Dina Surveys, Cité Verte Hospital, and GMC assurances, will meet once per year for input into trial progress and will be contacted between meetings as needed. Auditing of the intervention will take place consistently throughout the year via a qualitative study and quantitative data collection collected at midline. Staff from JHCP will be based at the hospital to help POWER participants navigate the healthcare system.

**Plans for communicating important protocol amendments to relevant parties (e.g., trial participants, ethical committees) {25}**

Any amendments to the protocol will be provided to the University College London Research Ethics Committee and National Ethics Committee in Cameroon and will also be communicated to all researchers on the project and project partners (JHCP, RENATA, HF, Dina surveys).

**Dissemination plans {31a}**

The project partners (JHCP, RENATA, HF, Dina surveys), the Ministry of Health in Cameroon, and the funders will be provided with a summary of the findings of the trial. The findings will also be reported in high-impact scientific journal articles and presented at scientific national and international conferences and in public forums as requested.

A national workshop at the end of the project will disseminate findings to national stakeholders (70+). Participants will include governmental organisations (Ministry of Health, CNLS), financial and technical partners (WB, USAID, ILO, GIZ, CHAI, AFD, UNICEF, WHO, CDC, UNFPA), researchers working on HIV/AIDS (University Yaoundé I, John Hopkins Cameroon Program), non-governmental organisations working with young women at high risk of HIV in Cameroon (e.g. Horizons Femmes, RENATA, CAMNAFAW, Alternatives Cameroun, Colibri, KidAIDS, SWAA littoral, Synergie des Sciences Sociales et Humaines, UFAPROD-M), and grassroots organisations of female sex workers. A policy brief will also be disseminated by those stakeholders through internal newsletters.

Throughout the lifetime of the project, accessible briefing notes will be created for the Institute for Global Health (UCL), the PI’s UCL webpage and social media (Twitter - <https://twitter.com/power_ucl>. A press release of research findings will be created upon publication which will be communicated with journalists in the general media (e.g., CNN). Digital stories will also be produced to engage the public on the effect of economic shocks on the sexual behaviours of young women in Cameroon. These digital stories will be presented in Cameroon and at the ESRC festival of social science in order to engage the public in this research.

